#### Design

Cluster randomised trial.

#### Setting

As per host pilot trial

#### Participants

As per host pilot trial

#### Intervention

Group 1: Participant recruitment at 35–36 weeks + 6 days gestation

Group 2: Participant recruitment at 37–38 weeks + 6 days gestation

#### Randomisation

To minimise the impact of the embedded SWAT on the design and conduct of the definitive trial, randomisation to the different timings of recruitment will be conducted at the site level, i.e. site randomisation. Each of the 2 sites will be randomised to recruit women from group 1 or group 2.

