## Methods/design

### Trial aim and objective

The primary objective of the MILO Study is to assess the feasibility of conducting a definitive randomised controlled trial to examine the effectiveness, and optimal intensity (timing and frequency), of membrane sweeping to prevent post-term pregnancy. The study consists of four work packages.
*WP1*: *a pilot randomised trial* assessing the feasibility of conducting a definitive trial to evaluate how often and the best time to perform a membrane sweep*WP2*: *health economic analysis* assessing the feasibility of conducting a trial-based economic evaluation to examine the cost-effectiveness of membrane sweeping*WP3*: *a qualitative study* exploring the acceptability of the trial for women and clinicians*WP4*: *a study within a trial (SWAT)* assessing if the point at which women are invited to take part in the trial (i.e. when should women be asked?) affects the number of women recruited to and retained in the trial

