#### Aim

To evaluate the effect of the timing of the invitation to women to take part in the trial on recruitment and retention.

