##### Secondary outcomes

Proportion of eligible women recruited. Data will be extracted from routinely collected data.Proportion of recruited women that complete trial. Data will be extracted from routinely collected data.

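### The SWAT allocates invitation timing by site with only two sites, so it cannot estimate the timing effect it sets out to evaluate

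*Protocol article*

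**What the plan says.** All references are to the Protocol article. Under Work package 4, Aim, the purpose is "To evaluate the effect of the timing of the invitation to women to take part in the trial on recruitment and retention". Trial aim and objective says the same thing: the SWAT asks whether the point of invitation "affects the number of women recruited to and retained in the trial". The Design entry reads "Cluster randomised trial".

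The two arms, under Intervention, are invitation at 35 to 36+6 weeks and at 37 to 38+6 weeks. Under Randomisation, "randomisation to the different timings of recruitment will be conducted at the site level, i.e. site randomisation", and then "Each of the 2 sites will be randomised to recruit women from group 1 or group 2". The reason given is to limit the SWAT's effect on the conduct of the trial. The Setting section of Work package 1 confirms that there are two hospitals, and the SWAT sample size is that of the host trial. No crossover between windows, randomisation within a site or further cluster is described.

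The SWAT's primary outcomes are an evaluation of the randomisation, allocation and concealment processes, and the estimation of parameters for later sample size planning. "Proportion of eligible women recruited" and the proportion of recruited women who complete the trial are secondary.

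**The concern.** The aim is causal, but the allocation gives at most one hospital to each window. Any difference in the proportion recruited or retained is then also a difference in staff, case mix, clinic flow and local willingness to take part. The plan itself treats centre as worth controlling: the host randomisation is stratified by centre, and the Control group section says that usual care is the same at both sites but still sets out to look for site-specific features of care.

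What is at stake is the choice of invitation window for the definitive trial, which could be made on a difference between two hospitals. The outcome hierarchy adds to the problem, because the two quantities named in the aim are not the SWAT's primary outcomes.

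**Working it through.** **The plan's own figure.** 66 women per site × 2 sites = 132, as stated in Sample size for pilot trial. The SWAT takes this over and has no sample size reasoning of its own.

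**Identifiability if the sites receive different windows.** At site level the design has an intercept, a timing term and a site term. The rows are (1, 0, 0) and (1, 1, 1). The timing and site columns are identical, so the rank is 2 for 3 parameters. Between-cluster degrees of freedom = clusters − arms = 2 − 2 = 0.

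**Randomisation inference.** With c sites per arm, the smallest two-sided permutation p is 2/C(2c, c), capped at 1:

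| Sites per arm | Smallest p | Between-cluster df |
|---|---|---|
| 1 | 1.00 | 0 |
| 2 | 0.33 | 2 |
| 3 | 0.10 | 4 |
| 4 | 0.029 | 6 |

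Under pure site-level allocation, four sites per arm are needed before p < 0.05 is even possible.

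**If each site is randomised independently, 1:1.** The chance that both draw the same window is 2 × ½ × ½ = 50%.

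**Illustrative size.** Two assumptions are needed. First, 30% of eligible women are recruited. This is the minimum in the progression criteria, not a forecast; it gives 132/0.30 = 440 eligible women, or 220 per site. Second, true site recruitment rates vary with an SD of 3, 5 or 8 percentage points. The documents give no such figure. There is taken to be no timing effect.

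- SD of the hospital difference that would be read as timing: √2 × SD = 4.2, 7.1 and 11.3 points.
- SE if women are treated as independent: √(2 × 0.3 × 0.7/220) = 0.0437.
- SE including site variation: √(0.0437² + 2 × SD²) = 0.061, 0.083 and 0.121.
- False-positive rate of a nominal 5% comparison of women as independent: 2 × [1 − Φ(1.96 × 0.0437/total SE)] = 16%, 30% and 48%.

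As a cross-check, these SDs correspond to ICCs of SD²/(0.3 × 0.7) = 0.004, 0.012 and 0.030. A beta-binomial simulation with 220 women per site gave 17.6% at ICC 0.005, 27.5% at 0.01, 40% at 0.02 and 58% at 0.05, which agrees.

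**Does a simple crossover solve it?** With two sites, two periods and opposite order there are four site-by-period proportions and four parameters (intercept, site, period, timing), so 4 − 4 = 0 residual degrees of freedom. It removes stable site differences but leaves site-by-period variation inestimable. With b blocks per site, the residual df are 2b − 2 (sites) − 1 (timing) − (b − 1) (periods) = b − 2, provided the two sites do not follow the same sequence. This gives 0 at b = 2 and 4 at b = 6.

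**The case against.** The strongest reply is that this is a small part of a feasibility study and that the protocol disclaims formal hypothesis testing, both in its feasibility outcomes and under Data analysis. That stands against the false-positive rates: they describe an individual-level test that nobody has planned, with assumed inputs. A reader might infer that the SWAT will produce false positives 16% to 48% of the time; the documents do not support that. The reply does not rescue the aim, because an estimate reported without a p-value is confounded in the same way.

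A reader might also infer that the SWAT compromises the pilot as a whole. It does not. Sweep versus no sweep is randomised by individual and stratified by centre, and none of the progression criteria (recruitment, completeness of outcome data, clinician willingness) uses the contrast between windows. Nor is the SWAT empty: its process outcomes can be assessed as written, and their listing as primary suggests that the authors saw it partly as a process pilot.

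That the sites will receive one window each is an inference, since the text does not require them to differ. The other reading is no better.

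Finally, site-level allocation has a stated reason, to limit the burden on the trial. That is a fair ground for not randomising individual women. It does not explain why a site should keep one window throughout.

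**Conclusion.** The design and the stated aim of Work package 4 contradict each other. With two sites and site-level allocation, the effect of invitation timing is either wholly confounded with hospital or, with probability one half under independent randomisation, not observed at all. This follows from the number of sites and the unit of allocation, and needs no assumption about recruitment rates or site variation. Because it is a matter of design, a separate analysis plan could not repair it.

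The consequence is limited to what the SWAT may conclude about timing. It should be fixed, but it is no obstacle to the host pilot. Only the illustrative sizes rest on the assumed 220 eligible women per site and site SDs of 3, 5 and 8 points.

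**What to change.** Choose one of two changes before recruitment opens; the article reports that it had not yet begun.

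(a) **Descriptive SWAT.** Reword the aim under Work package 4 and the matching line in Trial aim and objective as descriptive or feasibility. Report recruitment and retention by site, and state that no conclusion on the effect of timing will be drawn. The cost is wording only, and the timing question is given up.

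(b) **Randomised blocks within site.** Randomise several time blocks, or clinics, within each site to the two windows. Define block membership by something fixed in advance, such as the calendar period of the 39-week visit, and classify each woman by the window assigned to her block. Use all eligible women at the 39-week visit as the denominator under both windows. Compare within site with the block as the unit of analysis. Make the proportions recruited and retained the SWAT primary outcomes, so that they match the aim. A single two-period crossover is not enough.

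Option (b) needs no extra women. Its cost is overlap at each changeover, when packs for both windows must be handed out side by side within a 6-month recruitment period, and more of the site coordination that the protocol wished to keep low. If that is not acceptable, (a) is the honest choice.

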#### Recruitment

##### Identifying potential participants

Clinicians at participating antenatal clinics will identify potential participants that meet the study inclusion criteria. Written trial information will be offered to women potentially eligible for participation at 35–36^+6^ week’s gestation OR 37–38^+6^ week’s gestation, dependent on-site randomisation in the SWAT, during routine antenatal appointments. Women will be given an information pack, which will include a letter introducing the trial and a participant information leaflet, which will inform participants of the background and purpose of the study, risks and benefits of participation, what participants are being asked to do, their right to withdraw and offer to answer any questions they have relating to the study. This will be followed up at the 39-week antenatal visit when the researcher will invite eligible women to participate.

#### Obtaining informed consent

At the 39-week antenatal visit, potential for inclusion to the trial will be checked by the attending clinician and/or research staff. The attending clinician and/or research staff (we expect this will be the researcher unless at the request of clinical staff) will be available to explain the trial and answer any questions potential participants might have. Eligible women will be asked to participate at this time and written informed consent will be obtained from women agreeing to participate.

#### Outcomes

##### Primary outcomes

Evaluation of randomisation, allocation and concealment processes through focus group interviews and data extracted from routinely collected dataEstimate variable parameters to inform sample size for definitive trial, including standard deviation of the outcome measure

##### Secondary outcomes

Proportion of eligible women recruited. Data will be extracted from routinely collected data.Proportion of recruited women that complete trial. Data will be extracted from routinely collected data.

#### Sample size

##### As per host trial

Table 2 outlines the schedule of enrolment, interventions and assessments within The MILO Study.

**Table 2 Tab2:** Schedule of enrolment, interventions and assessments within the MILO Study

Time point	Study period					
	35–36^**+6**^ OR 37–38^**+6**^ weeks gestation (*dependent on SWAT allocation*)	39 weeks gestation	40 weeks gestation	41 weeks gestation	Postnatal period (*after last study participant is discharged from maternity*)	Postnatal period (*6 weeks after the last participant has given birth*)
**Eligibility screen and written information**	X					
**Informed consent**		X				
**Allocation**		X				

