#### Primary outcomes

The following are the outcomes relating to feasibility assessment:
Recruitment: evaluation of the number and percentage of eligible women who are recruited and randomised to the study. Assessed by study-specific checklists.Retention: evaluation of the number and percentage of eligible women who are randomised, take part in and adhere to the study protocols. Data will be extracted from routinely collected data.Adherence with the trial interventions: evaluation of adherence with the trial interventions and reasons for non-compliance assessed by study-specific checklists. Data will be extracted from routinely collected data and focus group interviews with clinicians and participants at 6 weeks post-intervention.Evaluation of the randomisation process: evaluation of effective allocation of participants to the intervention/control group assessed by study-specific checklists and evaluation of the randomisation protocol throughout the randomisation period.Evaluation of attrition rates: evaluation of attrition rates assessed by study-specific checklists. Data will be extracted from routinely collected data.Evaluation of the types of attrition: evaluation of the types of attrition assessed by case report forms. Data will be extracted from routinely collected data.Evaluation of the data collection process through study-specific checklists: evaluated, statistically and narratively, by assessing the completeness of the outcome measurements at baseline and postnatal (6 weeks) through study-specific checklists. Researchers will manually examine the data collected. They will assess the proportion of complete data collection forms, the quality of data collected and the applicability of this data in facilitating pilot trial outcomes.Estimate the main effect of individual intervention components and their interactions: estimates (with measures of uncertainty) of the main effect of individual intervention components and any interaction effect between the main effects of the embedded factorial design will be assessed and reported using regression analysis.Evaluation of the data analysis process: as this is a feasibility study, formal hypothesis testing will not be undertaken. Researchers will manually examine the data collected. Evaluation of the data analysis process will be undertaken through the assessment of gaps and limitations to the analysis process measured by study-specific checklists. Findings will be reported through descriptive statistics and graphical summaries.Evaluation of the EQ 5D: assessment of the mechanism of, timing of and delivery of the EQ 5D through study-specific checklists.Feasibility of cost analysis process through analysis of study-specific documentation: assessment of data collection tools to undertake cost-effectiveness analysis through study-specific documentation. Researchers will manually examine the data to assess the mechanism of, timing of and delivery of the cost analysis tools.Feasibility of the cost-effectiveness analyses: assessment of the mechanism and utilisation of the incremental cost-effectiveness ratio (ICER), through study-specific checklists.

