##### Neonatal secondary outcomes

Serious neonatal morbidity (e.g. seizures, birth asphyxia defined by trialists, neonatal encephalopathy, disability in childhood, proven and suspected neonatal sepsis)Apgar score < 7 at 5 minCord PH < 7.20: umbilical cord blood gas testNeonatal encephalopathy: (severity of hypoxic-ischaemic encephalopathy assessed using Sarnat staging: (i) stage 1 (mild)—hyper-alertness, hyper-reflexia, dilated pupils, tachycardia and absence of seizures; (ii) stage 2 (moderate)—lethargy, hyper-reflexia, miosis, bradycardia, seizures, hypotonia with weak suck and Moro reflexes; and (iii) stage 3 (severe)—stupor, flaccidity, small to mid-position pupils which react poorly to light, decreased stretch reflexes, hypothermia and absent Moro reflex)Perinatal death: (the perinatal period is defined as ‘commences at 22 completed weeks (154 days) of gestation and ends seven completed days after birth.’ [32])Admission to neonatal intensive care unit (NICU) or equivalent

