##### Trial

If IDMC requires termination of the study, e.g. futility analyses show no benefit to ongoing recruitment.

For the woman, the pilot trial is considered ended on discharge from the maternity hospital. For the infant, the pilot trial is considered ended on discharge from the maternity hospital or from the neonatal unit.

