**Intervention**						
**Group A**		X				
**Group B**			X			
**Group C**		X	X	X		
**Group D**			X	X		
**Qualitative study written information**					X	
**Focus group interviews**						X
**Qualitative study informed consent**						X
**EQ-5D-5L evaluation**		X			X	

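### Table 2 ties the only postnatal EQ-5D-5L to the last participant's discharge instead of each woman's own birth, so the pilot cannot assess the questionnaire at a defined time point

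*Protocol article*

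**What the plan says.** Table 2 (schedule of enrolment, interventions and assessments) has two postnatal columns, both defined by the last participant. One is headed "after last study participant is discharged from maternity", the other "6 weeks after the last participant has given birth". The row "EQ-5D-5L evaluation" is marked at 39 weeks' gestation and in the first of these columns. It has no mark in the second.

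Under Primary outcomes (Work package 1), data collection is to be judged "by assessing the completeness of the outcome measurements at baseline and postnatal (6 weeks) through study-specific checklists". A separate item in the same list makes the way the EQ-5D is delivered, and when, a feasibility outcome, without naming a time. Work package 2 bases the QALYs on the EQ-5D-5L, says the pilot will explore when and how to administer it, and states that no formal economic evaluation will be done.

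The Trial paragraph under End of trial discontinuation criteria says: "For the woman, the pilot trial is considered ended on discharge from the maternity hospital". It adds: "For the infant, the pilot trial is considered ended on discharge from the maternity hospital or from the neonatal unit". The Neonatal secondary outcomes include perinatal death, in a period that "ends seven completed days after birth", and give "disability in childhood" as one example of serious neonatal morbidity.

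**The concern.** A postnatal utility score has meaning only with a time since birth attached. If every woman answers after the last discharge, her interval is set by when she happened to enrol: the first women answer many months after birth, the last within days. The pilot lists EQ-5D timing among the things it is meant to find out. Spread produced by accrual is not a comparison of time points, so response, missingness and standard deviation would be estimated for a mixture that a definitive trial could not reproduce.

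The end-of-trial rule raises a second difficulty. The last discharge cannot precede a woman's own discharge, so under Table 2 every postnatal EQ-5D-5L falls after her participation has formally ended. The same rule, applied to infants, sits awkwardly with a death outcome that runs to day 7 and with an outcome example that belongs to childhood.

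**Working it through.** The plan gives no figure for the timing of the questionnaire, so there is none to reproduce. The check compares the passages and then sizes the spread.

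**Passages side by side**

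| Place | Postnatal time point | Anchor |
|---|---|---|
| Table 2, EQ-5D-5L row | after the last discharge | last participant |
| Table 2, final column (no EQ-5D-5L mark) | 6 weeks | last participant's birth |
| Primary outcomes, data collection item | 6 weeks | not stated; EQ-5D-5L not named |
| End of trial, woman | discharge | her own |

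No two of these rows give the same time point and the same anchor.

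**Inputs from the article**
- 132 women (Sample size for pilot trial).
- Recruitment over 6 months (same section), or February to September 2021 (Trial status). In days: 183; 212 (1 February to 1 September); 241 (1 February to 30 September).
- Randomisation at the 39-week visit.

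**Assumptions not in the article**
- Uniform accrual.
- Birth 0 to 21 days after randomisation.
- Hospital stay 1 to 5 days.
- Questionnaire answered at the moment of the last discharge.

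**Formula.** For woman *i*, time since birth at the questionnaire is tᵢ = (latest discharge date over all women) − (birth date of woman *i*).

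**Simulation results** (2,000 repetitions; averages)

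| Window | Minimum | Median | Maximum | Within 6 ± 2 weeks | Beyond 12 weeks |
|---|---|---|---|---|---|
| 183 days | 0.5 wk | 14.1 wk | 27.6 wk | 15.3% | 57.9% |
| 212 days | 0.4 wk | 16.0 wk | 31.7 wk | 13.2% | 63.4% |
| 241 days | 0.4 wk | 18.1 wk | 35.6 wk | 11.6% | 67.6% |

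A separate run with births within 2.5 weeks and a fixed 3-day stay gave maxima of 27.2 weeks (6 months) and 35.6 weeks (8 months), with 15.4% and 11.5% in the window.

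**Hand check.** With even accrual, the share in a 4-week window is roughly 4 divided by the recruitment period in weeks: 4/(183/7) = 4/26.1 = 15.3%; 4/(212/7) = 4/30.3 = 13.2%; 4/(241/7) = 4/34.4 = 11.6%. In women: 0.153 × 132 ≈ 20 and 0.116 × 132 ≈ 15. The standard deviation of a uniform spread is the period divided by √12: 26.1/3.46 ≈ 7.5 weeks and 34.4/3.46 ≈ 9.9 weeks.

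**Sensitivity**
- The heading says only that the contact comes after the last discharge. A fixed delay adds the same amount to every interval and leaves the spread unchanged.
- Moving the mark to the 6-week column would not help, because that column is also tied to the last participant. The range would become 6 weeks to about 27.6 − 0.5 + 6 ≈ 33 weeks, or 35.6 − 0.4 + 6 ≈ 41 weeks.

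**The case against.** The best reply is that the heading is a labelling slip. Both postnatal columns fit the qualitative study: Work package 3 invites women to focus groups once the last participant has been discharged, and that invitation occupies the same Table 2 column. No prose passage says the EQ-5D-5L goes out in one batch. This is plausible, and if it is right the spread disappears. But the table is the only place that schedules the questionnaire, it has no postnatal column tied to the individual woman, and no other passage supplies a time. The correction is needed on either reading.

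Stronger readings are tempting, and the article does not support them:

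- *QALYs cannot be built at all.* Work package 2 disclaims a formal economic evaluation and puts EQ-5D-5L timing under study. Poor interpretability and inflated variance are supported; impossibility is not.
- *The arms would be compared unfairly.* Randomisation is in permuted blocks stratified by centre and parity, so timing should be similarly distributed across arms.
- *The outcome section already fixes the EQ-5D-5L at 6 weeks.* That item concerns outcome measurements in general, does not name the instrument and does not say from whose birth.
- *Early neonatal deaths will be missed.* Only infants discharged before seven completed days are affected. Infants in a neonatal unit stay in the trial until they leave it, and no length of stay or death rate is given.
- *The 90% completeness criterion counts an outcome that cannot be collected.* The childhood disability item is an example in an open list, and the progression criteria do not list required fields.

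**Conclusion.** The concern holds for the EQ-5D-5L anchor. Table 2, the 6-week statement and the end-of-trial rule do not agree. As written, the schedule gives no woman a postnatal time point of her own. Under even accrual over 6 to 8 months, time since birth would range from under 1 week to about 27 to 36 weeks, with about 12 to 15% of women at 6 ± 2 weeks. The exact figures rest on the assumed accrual, birth interval and stay; the width of the range comes mainly from the recruitment period. That every postnatal EQ-5D-5L falls after the woman's own end of trial needs no assumption.

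What is lost is the pilot's ability to estimate response, completeness and variance at a defined time. The neonatal points are secondary: a possible gap before day 7 for infants discharged early, and one outcome example that cannot be observed by discharge. Overall this should be fixed, but it does not undermine the pilot's design or its target of 132 women.

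**What to change.** 1. In Table 2, add a postnatal column defined by time since each woman's own birth and move the EQ-5D-5L mark there. Six weeks would match the general postnatal time point under Primary outcomes; if the sponsor prefers another time, state it and align that section. The two existing columns can stay for the qualitative study.
2. In the Trial paragraph under End of trial discontinuation criteria, extend the woman's follow-up to that contact.
3. For perinatal death, define the infant's end of follow-up as the later of discharge (maternity hospital or neonatal unit) and seven completed days after birth.
4. Delete the childhood disability example, or mark it as not collected in the pilot.

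The cost is wording changes, rolling instead of batch dispatch, and a day-7 record check for infants discharged earlier. The number of questionnaires is unchanged. The Data Availability section says recruitment had not begun, so the change can be made before the first woman enters. Once early participants pass the chosen time point, their scores at that point cannot be recovered.
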